### Data Collection

#### Overview

The eRegistry used by health workers in the intervention and control arms will provide some of the data for outcome measurements. Independent trained project staff collected data regarding birth outcomes, antenatal care utilization, and referral care seeking from a subset of the population of registered pregnancies through a postpartum household survey. The postpartum household survey started in June 2019, 8 months after the commencement of recruitment. Data collectors were provided with a list of all pregnancies registered in the eRegistry that were beyond 28 weeks of gestation at a given point in time. The data collectors made biweekly phone calls to clients from 28 to 35 weeks, and weekly thereafter to ascertain whether the pregnancy was ongoing. Postpartum household visits for data collection were conducted within 8-14 days of childbirth. A paper-based structured questionnaire was used for data collection (Multimedia Appendix 1), focusing on the experiences of pregnancy and childbirth, health care interventions received, and health outcomes of the mother and the newborn. The infant’s weight was measured during the home visit; weight was measured in minimal clothing, and the weight of the clothes was subtracted from the total weight. Where possible, women’s finger-prick blood was used to measure hemoglobin. The questionnaires were checked for completeness and consistency by the data collectors’ supervisors, and women were interviewed again if needed. Data from the paper questionnaires are being made electronic, and consistency checks are performed by the study team after data entry.

#### Data Management

Data generated from this project are stored in the Government of Bangladesh’s server located at the office of the Directorate General of Health Services. For analysis purposes, an authorized data manager from the study team will extract predefined data from the server in a secure manner. Data from the postpartum household survey will be stored in locked cabinets in the icddr, b premises, with the personal identifiers removed and stored separately. Once these data have been entered digitally, the data manager will relink the eRegistry data with the postpartum survey data using the study ID. No other personal identifiers were available or were retained. The data will be saved in a password-protected computer. The data manager will share anonymous data sets with researchers for outcome analysis.

#### Statistical Methods

The primary analyses will be conducted as an intention-to-treat analysis, based on the allocation question rather than the actual site of antenatal care services, comparing the intervention arm with the control arm for all outcomes. Health worker characteristics such as gender, age, and education and health facility characteristics such as distance to referral unit, volume of pregnant women seen per month, digital competency, and internet connectivity will be presented. Pregnant women’s age, parity, socioeconomic status, and education will be presented as background characteristics. Primary analyses will be performed at the individual client level. Categorical variables will be analyzed using generalized linear models of the binomial family with a log link to estimate the relative risks and prevalence ratios. Random effects will be included to account for the inherent effect of clustering. Absolute and relative differences between the intervention and control groups with 95% CIs were calculated. Confounders will be adjusted for in the primary analysis only if there are important baseline imbalances (ie, when the effect measure changes by more than 5% when added to the model). Subgroup analyses will be performed based on categories defined as a priori, such as those related to demographic characteristics. We will present the equity analyses of the differential effectiveness across subgroups, including wealth quintiles, residence, educational levels, and employment status for each outcome. The imputation of missing data will be considered.

To understand the client base and their utilization of the health system, we will describe the client flow across providers, facilities, and arms of the trial. It is expected that some women will cross between the intervention and control clusters to receive health care services. Secondary analyses will be performed per protocol, where only the subset of women who remain in their assigned clinic type (ie, all visits are within the intervention group or control group) will be analyzed. We will perform a dose-response analysis (based on the proportion and number of visits to the intervention group) to assess whether there is a threshold or linear effect based on the increased utilization of intervention clusters. Finally, we will present population-level estimates of the impacts of the eRegistry if they were to be fully implemented in this community.

The study team will develop a code for analyses using dummy intervention or control allocation. A statistician not otherwise involved in the trial will conduct the final analyses using the actual allocations. All statistical analyses will be performed using statistical software such as Stata version 16 or later or RStudio version 1.2.1335 or later.

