**Methods:**

The eRegMat is a cluster-randomized controlled trial conducted in the Matlab North and Matlab South subdistricts in the Chandpur district, Bangladesh, where health facilities are currently using the eRegistry for digital tracking of the health status of pregnant women longitudinally. The intervention arm received 3 superimposed data-driven DHIs: health worker clinical decision support, health worker feedback dashboards with action items, and targeted client communication to pregnant women. The primary outcomes are appropriate screening as well as management of hypertension during pregnancy and timely antenatal care attendance. The secondary outcomes include morbidity and mortality in the perinatal period as well as timely first antenatal care visit; successful referrals for anemia, diabetes, or hypertension during pregnancy; and facility delivery.

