### Outcomes

The outcomes were formulated based on their relevance to the health system context and were meant to capture the potential effects of the specific DHIs under assessment. Data for the primary (Table 2) and secondary outcomes (Table 3) will be derived from the eRegistry’s client health records and through postpartum home visit interviews.

**Table 2 table2:** Primary outcomes, data sources, and definitions.

Primary outcome	Sources of data	Measurement sequence	Definition	Intervention subcomponents with most direct effect
Timely attendance at eligible ANC^a^ visits	Postpartum household survey	Registrations continuously at point of care Household visit after the completion of pregnancy	Proportion with timely attendance	Targeted Client Communication via SMS text message: ANC appointment reminders
Screening and management for hypertension in pregnancy	Case records from the eRegistry^b^	Registrations continuously at point of care	Proportion that has at least one ANC at a randomized health facility with: Blood pressure measurement at routine ANC visits, and Referred if blood pressure is high, or Referred if blood pressure is high outside of the routine ANC visit	Health worker clinical decision support Feedback dashboards with action items

^a^ANC: antenatal care.

^b^eRegistry: electronic registry.

**Table 3 table3:** Secondary outcomes, data sources and definitions.

Secondary outcome	Sources of data	Measurement sequence	Definition	Intervention subcomponents with assumed direct effect
Timely first ANC^a^ visit	Case records from the eRegistry^b^ Postpartum household survey	Registrations continuously at point of care Household visit after the completion of pregnancy	Proportion of women that have an ANC visit at or before 16 weeks among those with a home pregnancy registration before 16 weeks	Targeted Client Communication via SMS text message: ANC appointment reminders
High-risk women successfully referred to a skilled provider for additional care	Case records from the eRegistry Postpartum household survey	Registrations continuously at point of care Household visit after the completion of pregnancy	Proportion of women that received additional care during pregnancy among those that are referred for severe anemia, or hypertension or diabetes during pregnancy	Health worker clinical decision support Targeted client communication via SMS: Referral reminders, high risk, facility delivery reminders

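### For attendance outcomes, the number of intervention-clinic visits is partly the outcome itself, so the planned dose-response analysis shows a gradient even with no intervention effect

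*Protocol article*

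**What the plan says.** The Statistical Methods section of the protocol article makes intention-to-treat the primary analysis, by the clinic that determined allocation. It expects some women to cross between arms and adds three further pieces of work.

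- A per-protocol analysis of women for whom "all visits are within the intervention group or control group".
- A dose-response analysis "based on the proportion and number of visits to the intervention group", intended "to assess whether there is a threshold or linear effect based on the increased utilization of intervention clusters". No outcome is named or excluded.
- A closing statement that "we will present population-level estimates of the impacts of the eRegistry if they were to be fully implemented in this community".

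Under Outcomes, Table 2 lists "Timely attendance at eligible ANC" visits as a primary outcome, defined as "Proportion with timely attendance". The other primary outcome, hypertension screening and management, is defined through contact with the clinics ("Proportion that has at least one ANC at a randomized health facility"). Table 3 adds timely first ANC visit, by 16 weeks, as a secondary outcome.

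**The concern.** A dose should precede the outcome or at least be distinct from it. Visits to intervention clinics are among the visits that timely attendance counts. A woman who attends more has, by that fact, both a higher dose and a better outcome. Regressing one on the other gives a positive slope whether or not the digital interventions work. The same holds for timely first visit: a woman with no visit has dose zero at every clinic and fails the outcome.

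The per-protocol rule raises a related question. Each further visit is another chance to cross arms, so requiring all visits to stay in one arm removes frequent attenders more often than infrequent ones.

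The protocol expects crossover, so the intention-to-treat effect may be diluted. Readers would then look to these secondary analyses, and a gradient in visit count could be taken as evidence of effect.

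**Working it through.** **1. The plan's own figure, to confirm the inputs.** Sample Size gives 77 women or 140 contacts per cluster, an intracluster correlation of 0.1, and changes of 20% to 33% and 12% to 22%. Eligibility Criteria gives 30 and 29 clusters. A two-sided 5% level is assumed. The design effect is 1 + (77 − 1) × 0.1 = 8.6, so the effective sizes are 30 × 77 / 8.6 = 268.6 and 29 × 77 / 8.6 = 259.7. Power is 92.5% and 86.6%. With 140 contacts the design effect is 14.9 and power is 93.6% and 88.2%. The stated power above 80% is reproduced.

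**2. Null simulation of the count dose.** From the plan: 30 and 29 clusters of 77 women, mean timely attendance 20%, intracluster correlation 0.1. Assumed: 1 to 4 eligible visits per woman, between-woman correlation 0.2 within clusters, 30% of missed visits attended late, and crossover of 0 to 30% per visit. The true effect is zero. There were 400 replicates per scenario. The outcome is timely visits divided by eligible visits, and the slope is from ordinary least squares.

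| Crossover, intervention / control | Slope per visit, all women | Slope, intervention arm | Intention-to-treat difference |
|---|---|---|---|
| 0 / 0 | 0.100 | 0.163 | −0.002 |
| 20% / 20% | 0.128 | 0.158 | 0.000 |
| 10% / 30% | 0.134 | 0.161 | 0.002 |
| 30% / 10% | 0.124 | 0.157 | 0.002 |
| 20% / 20%, 30% of visits private | 0.133 | 0.154 | −0.001 |

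At 20% crossover, mean timely attendance at 0, 1, 2 and 3 intervention-clinic visits was 12.6%, 26.1%, 36.5% and 52.5%. Every replicate gave p < 0.05, but those tests ignored clustering, so this is not a calibrated error rate.

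**3. Closed-form check and sensitivity.** Take the intervention arm without crossover. Let q be the chance that a missed visit is attended late and π = 0.2. Mean eligible visits are 2.5 and the mean square is 7.5. The between-woman correlation, including cluster, is 0.1 + 0.9 × 0.2 = 0.28. Let s = q + (1 − q)π be the mean chance that an eligible visit is made, and v = (1 − q)² × 0.28 × 0.16 its variance across women.

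- Covariance of outcome and dose: (1 − q) × 0.16 × (1 + 1.5 × 0.28) = (1 − q) × 0.227.
- Variance of dose: 2.5 × (s(1 − s) − v) + 7.5 × (s² + v) − (2.5s)².

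With q = 0.3: s = 0.44, v = 0.022, covariance 0.159, variance 0.968, slope 0.159 / 0.968 = 0.164, against 0.163 simulated.

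This setting implies 2.5 × 0.44 = 1.10 visits per woman, fewer than the plan's 140 / 77 = 1.82. Matching 1.82 through more late visits needs q = (1.82 − 0.5) / 2 ≈ 0.66. Then s = 0.727, v = 0.005, covariance 0.0775, variance 1.183 and slope 0.066. Over all women, with the control arm at dose zero and f = 30/59 = 0.508, the slope is f × 0.0775 / (f × (1.183 + 1.82²) − (f × 1.82)²) ≈ 0.028. The covariance carries the factor (1 − q), so in this model the slope is positive unless every missed visit is made up late.

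**4. Proportion as dose.** Among women with at least one public visit the slope was about 0.00, with crossover independent of attendance. Coding women without visits as proportion zero brought it back to 0.14 to 0.17.

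**5. Per-protocol set.** The chance of staying in the set after n visits is (1 − c)ⁿ. At c = 20% this is 0.80, 0.64, 0.51 and 0.41 for one to four visits. It falls from 0.90 to 0.66 at 10% crossover and from 0.70 to 0.24 at 30%. At 20% in both arms, mean visits were 0.90 inside the set and 1.90 outside. Timely attendance fell from 19.8% overall to 16.6% in the set, and the arm difference stayed at 0.000. At 10% versus 30% crossover (intervention versus control) the set gave 18.6% versus 15.0%, or +3.6 points. Reversed, it gave 15.1% versus 18.3%, or −3.2 points.

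**The case against.** These are secondary analyses. The plan says it will assess whether a gradient exists; it does not commit to a causal claim. It names the proportion of visits as well as the count, and the proportion shows no built-in slope among women who attend. Pairing doses with outcomes and coding non-attenders could be settled in an analysis plan that is not shown. A per-protocol analysis alongside intention-to-treat is conventional.

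Most of this stands and limits the point. It does not rescue the count: the protocol itself names the number of visits as a dose and sets no outcome aside.

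Four stronger readings are tempting but unsupported.

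- That the gradient is near total. Defining timely as three or more visits gives 100% at three and four visits and a relative risk of 1.74 per visit, but the protocol contains no such rule.
- That the per-protocol comparison is biased. With equal crossover it is not, and the protocol gives no crossover rates.
- That the full-implementation estimate rests on these analyses. It follows them in the text, but the protocol does not say how it is derived.
- That an instrumental-variable estimate is a clean replacement. Any visit at an intervention clinic is itself attendance. SMS to women and dashboards for community workers also let allocation affect attendance without such a visit, so the exclusion restriction is doubtful.

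**Conclusion.** The point holds for the count dose with attendance outcomes: timely attendance at eligible visits and timely first visit. With no true effect, timely attendance rose by 0.10 to 0.13 per intervention-clinic visit over all women in the simulated scenarios. It rose by about 0.03 when late visits were increased to match the plan's contact ratio without crossover. Crossover, eligible visits, between-woman spread and late attendance are assumptions that set the size; the direction was the same in every scenario run. The simulation addresses attendance, not the hypertension outcome.

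The per-protocol rule lowers attendance in both arms and biases their contrast only if crossover differs by arm, by about +3.6 or −3.2 points at an assumed 10% versus 30%. The intention-to-treat primary analysis is unaffected. This should be corrected, but it does not threaten the trial's main result.

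**What to change.** - State that the number of intervention-clinic visits will not be used as a dose for timely attendance or timely first visit.
- Where a gradient is kept for other outcomes, use the proportion of visits among women with at least one visit, adjusted for total visits. Label it descriptive and non-randomised.
- Keep the per-protocol analysis as secondary, but define adherence by a single visit, such as the first, rather than by all visits. Report crossover by arm and say how women without visits are handled.
- A complier-average estimate with allocation as instrument is optional. If given, state that SMS and community dashboards may violate the exclusion restriction.

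The cost is a few sentences in the analysis plan and no new data. The attendance dose-response result is lost, and some intervals will be wider.

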#### Cluster Level

All government-run community clinics and family welfare clinics routinely providing antenatal care, delivery, or postnatal care services outside the referral health facility in the Matlab North and Matlab South Upazilas were eligible for the trial. Facilities were excluded if (1) there was no community health care provider or family welfare visitor to provide information on antenatal care visits in the previous month or (2) they reported fewer than five antenatal care visits in the previous month. Of the 72 health facilities in the study area, 59 (82%) were randomized (Figure 1). In total, 30 health facilities and 59 health workers were allocated to the intervention arm, whereas 29 health facilities and 64 health workers were allocated to the control arm (Figure 1).

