### Sample Size

Sample size was calculated based on the 2 primary outcomes using the following assumptions: (1) a cluster size of 77 women and 140 antenatal contacts in the randomized health facilities for a 21-month enrollment period; (2) a 20% coverage of timely antenatal care visits and 12% of women screened and managed for hypertension in the control group, based on data from the 2014 Demographic and Health Survey; and (3) an a priori intracluster correlation coefficient of 0.1, commonly reported for such process outcomes [20]. The given sample size will have more than 80% power to detect a minimum clinically significant change from 20% to 33% for timely antenatal care visits and from 12% to 22% for hypertension screening and management. The sample size was calculated using Stata 16 (StataCorp).

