### Blinding

Due to the nature of the intervention, it was not possible to blind facility-based health workers to the allocation. Community-based health workers registering and allocating pregnant women were blinded to the allocation status of their preferred health facility. The data collectors conducting the postpartum home interviews were blinded to the allocation of individual women. Researchers performing the final analyses will be blinded to group allocation.

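### The final analysts are described as blinded, yet the final analyses use the actual allocations with no mention of masked labels, and dummy-allocation coding cannot settle the covariate choice

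*Protocol article*

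**What the plan says.** Three statements in the protocol article bear on this.

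- Blinding: "Researchers performing the final analyses will be blinded to group allocation".
- Statistical Methods, last paragraph: "The study team will develop a code for analyses using dummy intervention or control allocation", followed by "A statistician not otherwise involved in the trial will conduct the final analyses using the actual allocations".
- Statistical Methods, on covariates: "Confounders will be adjusted for in the primary analysis only if there are important baseline imbalances". An important imbalance is then defined as one found "when the effect measure changes by more than 5% when added to the model".

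The article does not say whether the actual allocations carry coded labels, whether the covariate rule is built into the code written beforehand, or which variables are candidates for it. Age, parity, socioeconomic status and education are named only as background characteristics to be presented.

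**The concern.** The Blinding section and Statistical Methods describe the same task, the final analyses. One says that whoever performs it is blinded; the other gives that person the real allocation. Being uninvolved in the trial makes the statistician independent, which is not the same as blinded. A reader cannot tell which procedure applied, yet the trial report could claim a blinded analysis.

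The usual reassurance is that the code is finished on dummy data, so that nothing is left to decide. That is incomplete here. The covariate rule works on the treatment-effect estimate, so the primary model is settled only once the real allocation is in use, which is where the two sections disagree.

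Analyst blinding carries some weight in this trial. Facility health workers are not blinded, and Table 2 takes the hypertension outcome from eRegistry records that health workers enter at the point of care.

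**Working it through.** **Step 1. The statements side by side.**

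| Place | Who | Task | Allocation seen |
|---|---|---|---|
| Blinding | Researchers | Final analyses | None (blinded) |
| Statistical Methods, last paragraph | Study team | Writing the code | Dummy |
| Statistical Methods, last paragraph | Uninvolved statistician | Final analyses | Actual; masking not mentioned |
| Statistical Methods, covariate rule | Not stated | Confounders in the primary model | Actual, because the rule uses the effect estimate |

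Rows 1 and 3 conflict unless something unwritten is added. Row 4 cannot be completed under row 2.

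**Step 2. The plan's own power figure.** Inputs: 29 control and 30 intervention clusters (Cluster Level); from Sample Size, 77 women or 140 contacts per cluster, intracluster correlation 0.1, and changes of 20% to 33% and 12% to 22%. The article states no alpha; two-sided 0.05 is assumed.

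- Design effect = 1 + (m − 1) × ICC. For m = 77: 1 + 76 × 0.1 = 8.6.
- Effective sizes: 29 × 77 / 8.6 = 259.7 and 30 × 77 / 8.6 = 268.6.
- Power = Φ[(difference − 1.96 × SE0) / SE1], with SE0 pooled and SE1 unpooled.
- Timely antenatal care: (0.13 − 1.96 × 0.0385) / 0.0379 = 1.44, giving 92.5%.
- Hypertension: (0.10 − 1.96 × 0.0328) / 0.0323 = 1.11, giving 86.6%.
- For m = 140 the design effect is 14.9, and power is 93.6% and 88.2%.

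All agree with the stated figure of more than 80%. The present point changes none of them.

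**Step 3. What the covariate rule does.** This was simulated under a true relative risk of 1, with 29 and 30 clusters of 77 women, a 20% rate, an intracluster correlation of 0.1 and 2000 runs per setting. The analysis was a linear regression of the log cluster proportion. The following are assumptions and not in the documents: 4 or 6 independent cluster-level candidates, each with correlation r of 0.1, 0.2 or 0.3 with the latent cluster level of the outcome.

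| Candidates, r | Rule triggers any adjustment | Dummy allocation picks the same set | Type I, unadjusted | Type I, rule applied mechanically | Type I, free choice among those passing |
|---|---|---|---|---|---|
| 4, 0.1 | 40.5% | 47.9% | 4.0% | 4.5% | 5.3% |
| 4, 0.2 | 60.0% | 30.1% | 5.0% | 5.0% | 7.1% |
| 4, 0.3 | 82.2% | 14.4% | 4.7% | 4.2% | 8.4% |
| 6, 0.1 | 54.3% | 34.2% | 5.1% | 5.2% | 7.1% |
| 6, 0.2 | 75.9% | 15.1% | 5.1% | 5.4% | 9.0% |
| 6, 0.3 | 92.7% | 5.8% | 4.9% | 3.1% | 11.3% |

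The Monte Carlo standard error near 5% is √(0.05 × 0.95 / 2000) = 0.5 percentage points. The assumed candidates together explain between 4 × 0.1² = 4% and 6 × 0.3² = 54% of the latent between-cluster variance, so the last row is a generous case.

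**Step 4. Reading.** The dummy allocation reproduced the real covariate set in 6% to 48% of runs, so dummy coding cannot settle the model. Error inflation appears only in the last column, where the analyst is free to choose.

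**The case against.** The strongest reply is that the sections can be reconciled. The reference to actual allocations follows directly on the sentence about dummy ones, so it may mean only real as opposed to dummy, with labels still masked. Alternatively, the blinded researchers may be the study team, with the uninvolved statistician simply running their code. Both readings are possible but neither is written. The second is strained, because Statistical Methods gives the study team the coding and someone else the final analyses.

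It can also be said that a numeric threshold leaves no discretion: its outcome depends on the real allocation, but that does not mean an analyst chooses it. This stands. If the candidate list and algorithm are fixed in locked code, possibly in a full protocol or analysis plan not shown here, the simulation shows no inflation. The missing list is therefore not itself the fault.

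A reader might infer that an unblinded analyst will pick the primary model knowing which arm it favours, so that the primary result is unprotected and its type I error inflated. The document does not support this. It gives the statistician no stated freedom over covariates, and other safeguards remain: home-interview data collectors are blinded, as are the community workers who register and allocate women, and timely attendance is taken from the postpartum household survey. Nor would masking alone cure a free choice of model. A two-sided p-value is the same when the labels are swapped, so masking hides direction but does not limit selection.

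**Conclusion.** The point holds as a conflict of wording with a limited, conditional consequence. The article claims a blinded final analysis, and the procedure it describes does not deliver that as written. Dummy-allocation coding does not fully repair this, because the 5% rule needs the real effect estimate.

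The effect on type I error is nil if the rule runs mechanically from locked code (3.1% to 5.4% in the simulation). It is an illustrative 5% to 11% if the choice among passing covariates is discretionary. That range rests on assumed numbers of covariates and correlations, and on a cluster-level analysis in place of the planned log-binomial model with random effects. It illustrates the possible size and does not estimate what happened in this trial.

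**What to change.** 1. Reconcile Blinding with Statistical Methods by stating who is blinded, to what, and until when.
2. Before the actual allocations are used, lock the candidate covariates and the selection algorithm in the code. Alternatively, prespecify the covariates, for example the stratification and restriction factors under Randomization of Health Facilities: clinic type, staffing, allocation in the preceding project, staff technological skills, monthly clients and monthly antenatal visits.
3. Supply the actual allocations to the statistician as A/B codes, and break the code only after the primary results are locked.
4. If masking is not done, delete the claim of analyst blinding.

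Steps 2 and 3 are both needed: the first removes discretion, the second hides direction. The cost is a recoded allocation file and a few sentences. Masking would be imperfect, because the published counts of 30 and 29 facilities may partly reveal the arms if every cluster contributes data. Sample size and power are unaffected.
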